Smoking status		Do you smoke or did you smoke in the past? If yes, how many cigarettes per day and for how many years?	X		X	X	X
Alcohol use		AUDIT-C [59]	X		X	X	X
Social domain							
Caregiver burden		TOPIC-MDS [41]	X			X	X
Medication use							
Polypharmacy	+	Do you use five or more different medications?	X			X	
Medication adherence	+	Medication Adherence Questionnaire	X		X	X	X
Side effect of medication	+	Do you experience difficulties or side effects with medication use?	X			X	
Type of medication		Type, frequency and dose of medication	X^¶^		X^¶^	X^¶^	X^¶^
Physical performance							
Physical performance		30-s chair stand test [60]		X		X	
Mobility		SPPB [36]	X			X	
Physical capacity		2 MST [37]	X	X		X	
Perceived exertion		Borg RPE scale [61]	X	X		X	
Dyspnoea		MRC dyspnoea scale [62]		X		X	
Parameters							
BMI		Weight and length	X			X	
Waist circumference			X			X	
Blood pressure		mmHg	X			X	
Heart frequency		BPM	X			X	
Respiratory rate			X			X	
Blood parameters		Hemoglobin	X^¶^		X^¶^	X^¶^	X^¶^
		Albumin	X^¶^		X^¶^	X^¶^	X^¶^
		Creatinine	X^¶^		X^¶^	X^¶^	X^¶^
		Total cholesterol	X^¶^		X^¶^	X^¶^	X^¶^
		LDL-cholesterol	X^¶^		X^¶^	X^¶^	X^¶^
		HDL-cholesterol	X^¶^		X^¶^	X^¶^	X^¶^
		Triglyceride	X^¶^		X^¶^	X^¶^	X^¶^
		Glucose / HbA1C	X^¶^		X^¶^	X^¶^	X^¶^
Healthcare utilization		TOPIC-MDS [41]					
Readmission		Have you been hospitalized in the last six months? If yes, what was the hospitalization diagnosis and in what hospital were you readmitted?			X^¶^	X^¶^	X^¶^
Emergency visits		Have you visited the emergency or cardiac emergency room in the last six months? If yes, how many times and for what reason?			X*	X*	X*
Nursing home admission		Have you been admitted to a nursing home in the last months? If yes, for how many weeks?			X	X	X
General practice consult		Have you had a consult with your general practitioner in the last month? If yes, was this during office hours or during the evening, night or weekend and how many times in total?			X	X	X
Home visit of GP		Have you had a home visit from your GP in last month? If yes, was this during office hours or during the evening, night or weekend, and how many times in total?			X	X	X
Home care		Do you receive home care? If yes, is this care assistance and/or domestic help, and how many hours per week?			X	X	X
Day care		Do you have day care? If yes, how many days per week?			X	X	X
Cardiac rehabilitation use		Do you participate in cardiac rehabilitation in a rehabilitation center or outpatient clinic?			X	X	X

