Physical therapy		Do you participate in cardiac rehabilitation in a rehabilitation center or outpatient clinic?			X	X	X

*Abbreviations CCI* Charlson comorbidity index, *ALDS* Amsterdam linear disability scale*, NRS* numeric rating scale, *SNAQ* short nutritional assessment questionnaire, *MMSE* mini mental state examination, *GDS-15* geriatric depression Scale-15, *HADS-A* hospital anxiety and depression scale-anxiety subscale*,* EuroQol-5D Euroqol quality of life, *MDS* minimal dataset, *SPPB* short physical performance battery, *2MST* 2 Minute step test, *Borg RPE scale* ratings of perceived exertion scale, *MRC Dyspnea Scale* Medical Research Council dyspnea scale, *mmHg* millimetre of mercury, *BPM* beats per minute

*T0: baseline, ≤ 48 h after admission; ^†^T0+: within 2 weeks after hospitalization during home-based cardiac rehabilitation intake; ^‡^T1: 3 months after hospitalization, follow-up by telephone; ^§^T2: 6 months after hospitalization, follow-up by home visit; ^||^T3: 12 months after hospitalization, follow-up by telephone. ^¶^Data will be obtained from the medical record

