#### Secondary outcomes

Secondary outcomes will be measured at three, 6 and 12 months. Data will be collected by telephone at three and 12 months and at 6 months by a home visit of a blinded research nurse. Table 3 provides an overview of the data collection on different time points. The secondary outcomes are the following:The incidence of the first all-cause unplanned hospital readmission or mortality within 3 months and 12 months after randomization (triangulated by self-reporting and hospital data management system)Activities of Daily Living (ADL)- / instrumental ADL-functioning at 3*,* 6 and 12 months after randomization (the AMC Linear Disability Score) [35]Functional capacity at 6 months after randomization (Short Physical Performance Battery [36] and 2-min step test [37])Medication adherence (questionnaire and pharmacy dispensing records) at 3*,* 6 and 12 months after andomizationAnxiety and depression at 6 months after randomization (HADS-anxiety [38] and Geriatric Depression Scale-15 [39])Health-related quality of life at 6 and 12 month after randomization (EuroQol-5D-5 L) [40]Healthcare utilization at 3*,* 6 and 12 months after randomization (extension of *The Older Persons and Informal Caregivers Survey - Minimum Data Set (TOPIC-MDS)* [41] including readmission, emergency visits, GP visits, physical therapy and cardiac rehabilitation)Caregiver burden, at 6 and 12 months after randomization (TOPIC-MDS) [41]

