### Cost effectiveness analysis

We will perform a cost-effectiveness analysis from a societal perspective. Incremental cost-effectiveness ratios (ICERs) will be calculated by dividing the difference in total costs between the intervention group and the control care group by difference in readmission/mortality rates and Quality Adjusted Life Years (QALYs). The uncertainty surrounding the ICERS will be estimated with non-parametric bootstrapping (5000 replications). The intention to treat principle will be applied to analyse the data. Missing values for cost and effect data will be predicted by multiple imputation.

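### As printed in Table 3, the emergency-visit question at 3 months reaches back before baseline, and the physical therapy row asks about cardiac rehabilitation instead

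*Protocol article*

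**What the plan says.** Under Secondary outcomes, the protocol article lists healthcare utilization at 3, 6 and 12 months after randomization, "including readmission, emergency visits, GP visits, physical therapy and cardiac rehabilitation". Physical therapy and cardiac rehabilitation are thus two separate components.

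Table 3 (under Hospital care for all included patients) prints the questions and marks them for T1 (3 months), T2 (6 months) and T3 (12 months), with the same wording each time:

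- Emergency visits: "Have you visited the emergency or cardiac emergency room in the last six months? If yes, how many times and for what reason".
- Readmission: "Have you been hospitalized in the last six months", followed by the diagnosis and the hospital. These cells carry the mark for medical-record data.
- GP consults: "Have you had a consult with your general practitioner in the last month". GP home visits likewise: "Have you had a home visit from your GP in last month".
- Cardiac rehabilitation: "Do you participate in cardiac rehabilitation in a rehabilitation center or outpatient clinic". The physical therapy row carries the identical sentence.

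No healthcare-utilization row is marked for T0. The emergency-visit cells carry an asterisk, whose footnote is the definition of T0. As printed, no record source is stated for that item.

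The section Cost effectiveness analysis adds: "We will perform a cost-effectiveness analysis from a societal perspective".

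**The concern.** A follow-up count should start at baseline. A six-month recall asked three months after baseline cannot do that: it mixes earlier use with follow-up use, and the patient's answer does not separate them. Earlier use is unlikely to be negligible here. Acutely admitted patients are included, and an unplanned admission in the preceding six months is one route to eligibility (Study population).

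The physical therapy row has a different fault: it asks about something else. The sentence concerns current participation in rehabilitation at a centre or as an outpatient. A patient treated by a physical therapist at home or in a local practice can truthfully answer no.

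At stake are the 3-month emergency-visit result and the physical therapy result at all three contacts. If the cost analysis draws its resource counts from these questions, the corresponding cost items are affected too.

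**Working it through.** The plan states no figure on this point, so there is none to reproduce. The inputs are the contact times (3, 6 and 12 months) and the recall periods (six months for emergency visits, one month for GP items), all from Table 3 and its footnotes. Table 3 times contacts from hospitalization and the outcome list from randomization; the few days between them are ignored.

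**Emergency visits.** Window = (contact time - recall, contact time).

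- T1: (3 - 6, 3) = (-3, 3)
- T2: (6 - 6, 6) = (0, 6)
- T3: (12 - 6, 12) = (6, 12)

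At T1, 3 of the 6 months precede baseline. T2 and T3 meet at month 6 without gap or overlap: 6 + 6 = 12 months, each covered once. Months 0 to 3 fall in both T1 and T2.

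**Size at 3 months.** Let the visit rate be λ per month after baseline and kλ in the three months before. Then recorded / true = (3kλ + 3λ) / 3λ = 1 + k. The documents do not give k, so it is an assumption: k = 0.5, 1 and 2 give 1.5, 2 and 3. The index emergency visit adds up to one more per acutely admitted patient.

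**Effect on the comparison.** Pre-baseline use should be balanced by randomization, so the expected difference in mean counts is unchanged, but with added noise. A ratio is pulled towards 1. If the true rate ratio is ρ, the recorded ratio is (k + ρ) / (k + 1). Taking ρ = 31.5/44 = 0.716, the ratio implied by the sample size section for the primary endpoint, purely as illustration:

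- k = 0.5: 1.216/1.5 = 0.81
- k = 1: 1.716/2 = 0.86
- k = 2: 2.716/3 = 0.91

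A yes/no measure suffers most, because every acutely admitted patient who came through an emergency room can answer yes in either arm.

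**Who cannot be repaired from the questions.** With no T0 item there is nothing to subtract. Patients who die or are lost between T1 and T2 have only the T1 answer. Patients who miss T2 but reach T3 have (-3, 3) and (6, 12), so months 3 to 6 are unseen.

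**Physical therapy.** The two rows carry the same sentence, while the outcome list counts two components. The sentence is also in the present tense. A six-week course started at discharge would usually be over by 3 months, about week 13.

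**GP items.** Windows are (2, 3), (5, 6) and (11, 12): 3 of 12 months. The first is about weeks 8.7 to 13.0 (2 × 52.18/12 to 3 × 52.18/12).

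**The case against.** The strongest case for the plan is that little is lost where it matters most, and much of this stands.

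- *Totals.* A reader might infer that the yearly emergency count will be inflated by half, since the three windows add to 18 months against 12 (18/12 = 1.5). Nothing in the article says the three answers will be added. Using T2 for six months and T2 plus T3 for twelve gives clean totals for patients reached at both.
- *Readmission.* Its question has the same six-month window, so one might think readmission counts, or even the primary endpoint, are corrupted. They are largely protected: Table 3 marks the item as medical-record data, the readmission outcome is checked against hospital data, and the follow-up questions on diagnosis and hospital help to identify an index stay.
- *GP contacts.* One might say they miss the intervention period. That is exact only for the six-week core. The adverse-events section runs the intervention to 12 weeks, which the first GP window overlaps. A one-month recall trades coverage for accuracy in a sample that includes patients with MMSE 15–23; it is a design choice and not an error.
- *Misprints.* The asterisk on emergency visits may stand for the medical-record mark, in which case dated records could correct that item. The physical therapy row looks like a copying slip. The questionnaire itself is not shown, and the process evaluation is to record intervention delivery and usual care. So the article does not show that physical therapy goes unasked in the trial, only that the printed question does not ask it.
- *Costs.* The cost section does not name the source of its resource counts, so the link to costs is an inference.

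What remains is the 3-month emergency count, the patients without a T2 contact, and the physical therapy row.

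**Conclusion.** The point holds in a limited form. As printed, the T1 emergency-visit question cannot deliver the 3-month component of the utilization outcome: half its window precedes baseline, and at a constant rate the count is doubled before any index visit is added. The printed physical therapy question does not measure physical therapy. Both are named components of a secondary outcome, so this should be corrected, but the primary endpoint is not affected.

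The conclusion assumes that the case record form uses the wording of Table 3 and that emergency visits are self-reported, as the printed marks suggest. The factor of 2 further assumes equal visit rates before and after baseline. The documents do not support the broader claim that the whole utilization outcome and the cost analysis will be miscounted.

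**What to change.** First compare Table 3 with the case record form. If the form is right, correct the table and state the data source for emergency visits. If the form matches the table:

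- At T1, ask about emergency visits and admissions *since you left hospital on [discharge date]*. Do not mention randomization, because patients are blinded to their assignment and receive only general information about the study.
- At T2, ask *since our contact on [T1 date]*. Alternatively, keep the six-month wording at T2 and T3 and state that T1 answers do not enter the 6- and 12-month totals.
- For patients already past T1, date emergency visits from hospital records and count only those after baseline.
- Replace the physical therapy row with a neutrally worded question on whether physical therapy was used and for how many sessions. Ask it after the other outcome measures, since the answer could hint at allocation to the blinded research nurse.

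The GP items can stay as they are. Home care and day care ask for current hours or days per week and have no recall window to change.

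The cost is a small change to the form and the nurse instruction, a record check for patients past T1, and a small residual risk of unblinding. Follow-up is expected to run to December 2019, so later contacts would benefit.

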### Intervention

The CCB program encompasses three phases of the care process: 1) clinical phase, 2) discharge phase from hospital to home and 3) post-clinical phase after hospital discharge. The intervention consists of three components: 1) case management, 2) disease management and 3) home-based cardiac rehabilitation. Medication management is an important topic in the three phases of the CCB intervention and is part of all three components.

### Phase 1: Clinical phase

Patients randomized to the intervention group will receive an integrated care plan based on geriatric and cardiac conditions identified by the CGA. This plan will be developed by the CRN together with the patient as follows. The CRN discusses identified health issues, asks if the patient recognizes them and what issues they prioritize for treatment. The integrated care plan is used to prioritize care during the three phases of the intervention. In case of ≥ 1 health issue in the psychological domain or ≥ 5 potential health issues in total, the geriatrician will be consulted. If indicated, the CRN also consults with other disciplines.

### Phase 2: Discharge phase

At least one day before discharge, the CCRN visits the patients to discuss and prepare discharge to home. A personalized face-to-face handover between the CRN and the CCRN is completed using a standardized discharge checklist. In case of logistical difficulties the handover is performed by video call via tablet. The CGA, integrated care plan and ongoing interventions are discussed. In addition, the current medical condition, medication prescriptions and therapy advices a patient needs to adhere to (e.g. fluid restrictions in case of heart failure) are discussed. Finally, the CRN contacts the primary care PT by telephone to arrange home-based cardiac rehabilitation.

### Phase 3: Post-clinical phase

After discharge home, the CCRN and PT continue care at home. The focus of these visits is in the first month post-discharge since this is when patients are at highest risk for readmission, mortality and functional decline [2, 3]. The CCRN visits the patient four times post-discharge; within 2 days, at 1, 3 and 6 weeks and if needed one more visit within 12 weeks post-discharge. During all home visits, the CGA, the integrated care plan and patients’ current medical condition is evaluated. During the first home visit medication reconciliation is performed by the CCRN to obtain the most accurate possible list of a patient’s current medications [29, 30]. This is done by comparing all the medications that the patient is taking (including over-the-counter drugs, herbals and vitamins) to those listed in the provided medication records (medication overview from the community pharmacy and the discharge summary from the hospital). Within 48 h after discharge the discharge summary, which contains an overview of the medications at discharge, reasons for changes in medication and results of diagnostic tests is sent from the hospital to the CCRN and pharmacist who is part of the research team.

In Table 2, the home visit schedule is presented, including specific themes during the home visits. The CCRN is allowed to deviate from the home visit schedule if indicated, for example because of changes in patients’ health status. During the home visits, the CCRN will indicate and refer if there is a need for additional care (domiciliary or otherwise) during or after the intervention period. For specific questions related to patients’ health status or medication discrepancies identified during medication reconciliation, the CCRN has access to the cardiac team of the hospital, the general practitioner (GP), pharmacist according to local communication routes or protocols of the hospitals. During the home visits the CCRN observes signs and symptoms of actual or potential drug-related problems (DRP), such as side-effects and inappropriate medication use (e.g. nonadherence) by using a recently developed instrument (Additional file 2. Adapted Red Flag instrument) based on the Red Flag instrument by Sino et al. [31] The observed problems are documented by the CCRN in the Adapted Red Flag instrument and evaluated by the pharmacist-investigator who has identified DRP and proposed suitable solutions. Subsequently the CCRN discusses these DRP and proposed solutions with the responsible healthcare providers.

The PT provides two home-based cardiac rehabilitation sessions per week during the first 6 weeks post-discharge. This program is based on therapy advices according to the Dutch multidisciplinary guideline of cardiac rehabilitation [32]. Depending on the patient’s functional status a stepwise graded exercise approach will be followed, starting with low intensity functional rehabilitation (class IV or higher on the Specific Activity Scale [33]) to the Metabolic Equivalent of Task level [34] (MET-level) needed for their goals and desired activities, as described in the rehabilitation plan. Exercise therapy will be adapted to comorbid diseases according to current guidelines. Within the last 2 weeks of the rehabilitation program, patient’s functional status will be evaluated. The CCRN and PT work in close collaboration during the intervention to tailor care and to evaluate progress. They have a joint home visit in the first week after discharge to verify and agree on the integrated care plan in relation to patients’ priorities.

In case of readmissions to participating hospitals and wards during the study follow-up of 12 months, patients will repeatedly receive the CCB program with exception of the rehabilitation exercise component. This is due to the limit on physical therapy sessions funded by Dutch healthcare insurance policies.

### Usual care

Patients in the control group will receive usual care during hospitalization and after discharge. During hospitalization, other disciplines are consulted as needed. The control group may receive geriatric care if the patients’ treating physician consults the geriatric team. All participating hospitals have a geriatric consultation team that can be consulted by the patients’ treating physician on indication. After discharge, care as usual may include medical care by a cardiologist according to the national cardiovascular guidelines and a cardiac nurse specialist, if available. Also, control group patients can be referred to center-based cardiac rehabilitation. According to the Dutch multidisciplinary guideline of cardiac rehabilitation, center-based cardiac rehabilitation consists two one-hour exercise sessions per week during 6 weeks [32]. However, it is expected that only a small number of patients in the control group will receive center-based cardiac rehabilitation due to their age, illness and clinical complexity.

Standard primary care will be provided in both the intervention and the control group. For non-cardiovascular problems, the GP is the primary healthcare provider. Optional care provision in the GP practice includes secondary prevention, medication titration, regular evaluations of physical health status and referral to other disciplines. In both groups the GP will be informed about the hospitalization by a discharge letter from the medical specialist. In the intervention group the GP is informed about the patients’ study participation by letter. During the intervention, the CCRN will be an extra liaison between care providers in case of medical, mental or social issues.

In the Netherlands virtually all citizens have basic healthcare insurance, which includes coverage of primary care visits, hospital outpatient visits, hospitalizations and prescribed medication. Dutch citizens can also purchase optional supplementary insurance, which includes physical therapy and other services.

### Training for healthcare providers and implementation

The CCB program combines case management, disease management and home-based cardiac rehabilitation, which require additional skills of healthcare providers. The participating CRNs and CCRNs will therefore follow a 5-day training program focussing on case management and disease management which addresses geriatric conditions, the performance of the CGA, development of an integrated care plan, pathophysiology of common cardiac diseases, early detection of physical deterioration and complications, pharmaceutical treatments and cardiac rehabilitation, including lifestyle counselling [9–13]. The participating PTs followed 2,5 day of the 5-day training program together with the CRNs and CCRNs, focussing on pathophysiology of common cardiac diseases, early detection of physical deterioration and complications, pharmaceutical treatments and cardiac rehabilitation, including lifestyle counselling.

We performed a feasibility process in six participating hospitals from June 2016 until May 2017 to check for potential inclusion rates to implement the study protocol and to train CRNs in data collection. In total 45 patients were included in this pilot phase. After successful implementation, we started the official inclusion stepwise per hospital with the first hospitals starting in June 2017.

### Sample size calculation

The sample size calculation is based on findings in a relevant subpopulation (101/674) of cardiac patients of the Transitional Care Bridge program [17], a comparable study including hospitalized patients ≥ 65 years at high risk of functional decline. Based on a six-month incidence rate of 44% (readmission and mortality combined) in the usual care subpopulation of the Transitional Care Bridge program and a minimal important difference of 12.5% in absolute risk reduction (from 44 to 31.5%) in patients in the intervention arm, (2-sided alpha of 0.05; power of 80%), a sample size of 235 patients per group is required. To compensate for an assumed 5% loss to follow-up, the total sample size per group will be 250 (Fig. 1).

